| Version 1.8 | 08-Nov-2023 | 
1. Administrative changes to Section 3.0 and 9.1 to further clarify that the MDRI is part of the method for determining need for dose escalation (i.e., Phase 2 primary outcome).
 
 
- Section 3.0 Added wording to elaborate that primary objective #2 is “a means to determine need for dose escalation.” Added further elaboration that this is because of the clinical heterogeneity of the population: “Due to the inherent heterogeneity of disease presentation, the MDRI will measure change tailored to patient-specific symptoms. MDRI change will inform dose-finding by reflecting lack of change in clinical outcome. The MDRI will be composed of the following:”
 
 
Rationale: Received feedback that wording is unclear as to relationship of MDRI to dose finding.
 
 
- Section 9.1 Added wording to clarify that the Primary Endpoint for the Phase 2 is dose finding: “Need for dose escalation as determined by within individual change over 8-week treatment period compared to change over 8-week observational period in the 2 most bothersome symptoms for each enrolled patient, selected from measures for the MDRI.”
 
 
Rationale: Received feedback that wording is unclear as to relationship of MDRI to dose finding.
 
2. Administrative changes in Section 2.2 to reflect change in title from Assistant Professor to Associate Professor for [name].
 |

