### 3.0 Objectives

The primary objectives of the study are to:

1. Evaluate the safety and tolerability of anakinra in children age  $\geq 4$  years with MPS III, defined by the incidence of treatment-emergent adverse events and abnormal laboratory values, and number of subjects withdrawn due to intolerability (e.g. unable to administer SC injection to subject, worsening behaviors).
2. Evaluate the effect of anakinra on a multi-domain responder index (MDRI) as a means to determine need for dose escalation. Due to the inherent heterogeneity of disease presentation, the MDRI will measure change tailored to patient-specific symptoms. MDRI change will inform dose-finding by reflecting lack of change in clinical outcome. The MDRI will be composed of the following:
  - Sanfilippo Behavior Rating Scale (SBRS)
  - Child Sleep Health Questionnaire (CSHQ)
  - Autism Parenting Stress Index (APSI)
  - PROMIS Fatigue - Parent Proxy Custom Short Form
  - Seizures – parent reported frequency, duration, and severity
  - Movement disorder (e.g. dystonia, chorea, etc.) – parent reported frequency, duration, and severity
  - Non-communicating Children's Pain Checklist-Revised (NCCPC-R)

The secondary objectives of the study are to evaluate the effect of anakinra on:

- Individual Clinical Response (ICR) – 5 most impactful clinical problems reported by the caregiver
- Gait
- Stair climb/descent
- Sleep Diary (1-week recall)
- Sanfilippo Syndrome Stool Habit Questionnaire

The exploratory objectives of the study are to evaluate the effect of anakinra on:

- ☐ Stool microbiome
- ☐ Vineland Adaptive Behavior Scales, Third Edition (VABS-III)

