## 8.0 Study Timelines

- The duration of an individual subject's participation in the study will be 52 weeks.
- The duration anticipated to enroll all study subjects is 1 year.
- The estimated date for the investigators to complete this study (complete primary analyses) is 3 months after the last subject's Week +8 visit.

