## 9.0 Study Endpoints

### 9.1 Primary and secondary endpoints.

#### Primary endpoints:

Phase 1: Incidence of treatment-emergent adverse events and laboratory values over 8 weeks of treatment to known frequency of anakinra-related AEs in other populations.

Phase 2: Need for dose escalation as determined by within individual change over 8-week treatment period compared to change over 8-week observational period in the 2 most bothersome symptoms for each enrolled patient, selected from measures for the MDRI. Choices are below in bold. These 2 symptoms will be monitored by one or more of the assessments below. If the Minimal Clinically Important Difference (MCID) that is defined below is not achieved after 8 weeks of treatment, or there has been a decrease of more than the MCID between 8 and 16 weeks after an increase greater than MCID at week 8, the dose will be escalated (see Section 27.7). If the MCID is not achieved after 8 weeks on maximum trial dose of 200mg (max dose 8 mg/kg/day), treatment with anakinra may be discontinued (see Section 27.7).

- Sanfilippo **Behavior** Rating Scale (SBRS): MCID = 0.25 SD for each scale
  - Symptoms described in table below:

|                         |                                                                                                                                        |                           |
|-------------------------|----------------------------------------------------------------------------------------------------------------------------------------|---------------------------|
| Body Movements          | Makes large complex movements of their body, such as spinning, twirling or repeatedly bouncing up and down.                            | Movement                  |
| Object Interaction      | Examines or manipulates some novel or unfamiliar objects repeatedly.                                                                   |                           |
| Activity/Routines       | Never plays with one object or engages in one activity for very long.                                                                  |                           |
| Emotional Function      | Expresses emotions inappropriate to the situation.                                                                                     | Social/emotional function |

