### **27.7 Dosing**

In this study anakinra subcutaneous (SC) will be administered at a dose level of 100 mg SC once daily. Anakinra will be administered every other day in patients who have severe renal insufficiency or end stage renal disease (defined as creatinine clearance < 30 mL/min as estimated from serum creatinine levels).

**Dose will be increased to 200 mg SC once daily**, with a maximum dose limit of 8 mg/kg/day, at **Week +8** if the change in at least one of the two most bothersome outcomes selected by the parents/guardians at the Day 1 visit has not improved by  $\geq$  the MCID as defined in Section 9.1. If the MCID is not achieved after 8 weeks on maximum trial dose of 200mg (max dose 8 mg/kg/day), **treatment with anakinra may be discontinued after a review and discussion between the study PI and subject's parent(s) of their child's individual results from all study outcome measures.**

**Dose will be increased to 200 mg SC once daily**, with a maximum dose limit of 8 mg/kg/day, at **Week +16** if the change in at least one of the two most bothersome outcomes selected by the parents/guardians at the Day +1 visit have worsened by  $\geq$  the MCID as defined in Section 9.1 between week +8 and week +16, after an improvement from Day +1 to week +8. If the MCID is not achieved after 8 weeks on maximum trial dose of 200mg (max dose 8 mg/kg/day), **treatment with anakinra may be discontinued after a review and discussion between the study PI and subject's parent(s) of their child's individual results from all study outcome measures.**

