**For example:**

- At week +8, if a subject has not improved in the chosen items then the dose will be increased to 200 mg SC daily.
- At week +8, if a subject has improved, then the dose stays at 100 mg SC daily. However, if this individual then has worsening of the two most bothersome outcomes from week +8 to week +16, after improving from day 1 to week +8, the dose will be increased to 200 mg SC daily at that point (i.e. increase at week +16 after not increasing at week +8).

**Dose will be decreased by 50 mg SC once daily** at any time throughout the study if a participant develops any of the following:

- Neutropenia  $<1200$  cells/microliter persistent for  $\geq 2$  weeks
- Thrombocytopenia  $<50 \times 10^9$  platelets/liter persistent for  $\geq 2$  weeks
- Mild/moderate hypersensitivity reactions including urticaria, rash, and pruritis
- Participants develops a CTCAE grade 3 AE

**Anakinra will be stopped** if the AE above does not resolve within 2 weeks of decreasing the dose by 50 mg SC once daily. Anakinra will be restarted at 0.5 times the last dose administered once the AE is resolved. If the AE recurs with restarting anakinra, it will be discontinued and the subject monitored per protocol.

The starting dose is the same dose level as recommended for adult rheumatoid arthritis patients. The dose escalation is within the range of the recommended dose in Neonatal onset multisystem inflammatory disease (NOMID), including also pediatric patients, is related to body-weight, with a recommended starting dose of 1-2 mg/kg up to a maximum dose of 8 mg/kg.

Smaller children with lower body weight need higher dose levels/kg body-weight in order to achieve similar anakinra serum exposure as in older, heavier children, due to a higher capacity to eliminate anakinra/kg body-weight, based on pharmacokinetic data in 22

systemic-onset juvenile idiopathic arthritis (SJIA) pediatric patients in the age range 2-17 years.

As an example, based on this study, a patient with a body-weight of 20 kg is predicted to require a dose of 4 mg/kg/day to achieve similar anakinra exposure (area under the curve [AUC]0-24h, ss and Cmin, ss) as a dose of 100 mg in a 50 kg patient. Additional examples are given below:

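### Need for dose escalation, the Phase 2 primary endpoint, measures only whether the starting dose is adequate, yet section 3.0 says it informs dose-finding

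*Protocol*

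**What the plan says.** Section 3.0 gives the second primary objective as the effect of anakinra on the MDRI, as a way to determine whether the dose must be raised, and adds: "MDRI change will inform dose-finding by reflecting lack of change in clinical outcome". The version 1.8 entry in section 1.0 describes the matching edit to 9.1: "Added wording to clarify that the Primary Endpoint for the Phase 2 is dose finding". The current text of 9.1 does not use the term dose finding. It defines the Phase 2 primary endpoint as "Need for dose escalation as determined by within individual change over 8-week treatment period compared to change over 8-week observational period", in the two most bothersome symptoms.

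All children begin on one dose (27.7): "In this study anakinra subcutaneous (SC) will be administered at a dose level of 100 mg SC once daily". Section 9.1 escalates if the minimal clinically important difference (MCID) "is not achieved after 8 weeks of treatment, or there has been a decrease of more than the MCID between 8 and 16 weeks", the second trigger applying after an improvement at Week +8. Section 27.7 words the Week +8 trigger as "the change in at least one of the two most bothersome outcomes selected by the parents/guardians at the Day 1 visit has not improved" by the MCID. Its example describes the later trigger as an "increase at week +16 after not increasing at week +8".

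Outcome on the higher dose appears in two places. Sections 9.1 and 27.7 say treatment may be discontinued if the MCID is not reached after 8 weeks on the maximum trial dose. The secondary endpoints in 9.1 cover an 8-week window on whichever dose was the highest effective and tolerated one for that child. On timing, section 8.0 says: "The estimated date for the investigators to complete this study (complete primary analyses) is 3 months after" the last subject's Week +8 visit.

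**The concern.** A dose-finding endpoint is normally expected to say something about how outcome varies with dose. This one is fixed in each escalated child before the first higher dose is given, and a child who meets neither trigger never receives the higher dose. A result that x of 20 children needed 200 mg would be equally likely if 200 mg were inert. With the wording of 3.0 beside it, such a count could be read as support for the higher dose, although it speaks only to the lower one. Nor do the secondary endpoints fill the gap, because their window pools children on different doses.

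**Working it through.** **1. Timing of each decision**

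| Decision | Scores used | Dose taken up to then |
|---|---|---|
| Week +8 trigger | change to Week +8 (9.1 also compares with the 8-week observation period) | starting dose only |
| Week +16 trigger | Week +8 to Week +16, only in children not escalated at Week +8 | starting dose only |
| Neither trigger met | as above | higher dose never given |

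No row contains a score obtained on the higher dose, so the distribution of the endpoint cannot depend on that dose's effect. This is structural and needs no assumption about effect size.

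**2. Illustration by simulation.** 400,000 children were simulated, each with two chosen outcomes. The MCID was 0.25 SD, the value 9.1 gives for several scales. Assumed: test-retest reliability 0.6, 0.75 or 0.9; correlation 0.3 between outcomes; starting-dose effect 0 or 0.25 SD; 200 mg effect 0 to 1 SD. With reliability 0.75 and no starting-dose effect, the share escalated by Week +16 was:
- 97.6% at every 200 mg effect, if both outcomes must improve to avoid escalation;
- 82.5% at every 200 mg effect, if one improved outcome is enough.

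The levels depend on the assumptions; the lack of any response to the 200 mg effect does not.

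**3. The plan's own precision figures (12.3, n = 20)**
- Binary: 13% to 18% at proportions of 5% to 15%. The Wilson interval with continuity correction gives half-widths of 13.3% and 17.5%, close agreement.
- Continuous: t(0.975, 19)/√20 = 2.093/4.472 = 0.468 SD, about the half SD stated.

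Neither figure concerns a comparison of doses.

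**4. Precision for escalated children only** (the number escalated is an assumption)
- Proportion near 50%, exact 95% half-width: 31 points with 10 children, 26 with 15.
- Mean change, t/√n: 2.262/√10 = 0.72 SD of change; 2.145/√15 = 0.55 SD of change.

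**5. Can change from Week +8 and change from Day 1 together isolate the added effect?** Take one outcome with SD 1 and reliability 0.75. Error variance is 0.25 per visit, so a change has SD √0.5 = 0.707. Suppose the higher dose adds nothing, and a child is escalated when the Day 1 to Week +8 change is below 0.25. Selection lowers the mean change by 0.707 × φ(z)/Φ(z), split equally between a low Week +8 error and a high Day 1 error.
- Assumed starting-dose effect 0.5 SD: z = (0.25 − 0.5)/0.707 = −0.354; 0.707 × 0.375/0.362 = 0.732; half is 0.366. Change to Week +16 is +0.37 from Week +8 and 0.5 − 0.366 = +0.13 from Day 1. Both exceed the true increment of zero.
- No starting-dose effect: z = +0.354; 0.707 × 0.375/0.638 = 0.415; half is 0.21. The changes are +0.21 and −0.21.

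The pair straddles the truth in the second case and misses it in the first.

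**6. Chance responders.** In the simulation with no drug effect at either dose, about 7% to 12% of Week +8 escalators (both outcomes must improve) or 36% to 46% (one is enough) still met the MCID at Week +16 against Day 1.

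**7. Schedule and dose.** A child escalated at Week +16 reaches 8 weeks on the higher dose at Week +24, when only safety laboratory tests are planned; outcome forms follow at Week +36. The 8 mg/kg/day limit keeps a child under 200/8 = 25 kg below 200 mg, so the higher dose is not a single dose.

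**The case against.** The best defence is that the protocol asks only what its endpoint answers. The objective in 3.0 is need for escalation, and the disputed sentence says the information comes from lack of clinical change, which is non-response. Section 9.1 never uses the term dose finding, no test of 200 mg against 100 mg is planned, and the sample size rests on feasibility. All of that stands, and it reduces the point to what the endpoint may be said to show.

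Four stronger readings are tempting and are not supported:
- **That no higher-dose data are collected.** Outcomes are scheduled at Weeks +16 and +36, and a secondary endpoint and a discontinuation check use them.
- **That the protocol claims the endpoint shows 200 mg works.** It nowhere says so. The risk lies in how the count may be read.
- **That the endpoint has power equal to the significance level for a dose difference.** There is no such test for that statement to describe.
- **That the log contradicts the current text.** The log agrees with 3.0 in purpose.

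The defence could add that a table split by dose is usually left to the analysis plan. That is fair as to its absence. The protocol does, however, itself fix the objective, the endpoint and the dose-mixing secondary window, and those are what need correcting.

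The timing in section 8.0 is weak support only. Its anchor is the Week +8 visit, but three months later is roughly Week +21, so Week +16 data from the last child could exist by then.

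**Conclusion.** The point holds in a limited form. The Phase 2 primary endpoint describes adequacy of the starting dose and carries no information on what the higher dose adds, while 3.0 presents it as informing dose-finding. The conclusion rests on the decision times in 9.1 and 27.7 alone. The simulated percentages and the number escalated are assumptions used to illustrate it. No numerical result in the protocol is wrong on this account; the fault is in what the endpoint is said to inform, together with a secondary window that pools doses.

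A reader might infer that reporting change from Week +8 beside change from Day 1 would bracket the added effect of the higher dose. It would not. The first is inflated by selection at Week +8, the second includes the starting-dose effect, and both carry time and open-label effects in a single-arm trial.

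**What to change.** - **Section 3.0:** replace the dose-finding sentence with a statement that the endpoint describes adequacy of the starting dose and gives no evidence on the effect of the higher dose.
- **Section 9.1:** say the same beside the Phase 2 primary endpoint, keeping the comparison with the observation period.
- **Secondary analyses:** report children separately by dose actually received, in mg and in mg/kg. For those escalated at Week +8, give the number reaching the MCID and the mean change at Week +16, from Week +8 and from Day 1, each with a 95% interval. Label the table descriptive and print the limits named in the verdict beneath it.
- **Sections 9.1 and 27.7:** the rule in 27.7 turns on at least one of the two outcomes not having improved, whereas its example speaks of no improvement in the chosen items. These passages must be reconciled so that the count is defined. So must the comparison with the observation period, which 9.1 makes and the 27.7 rule does not.

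The table uses forms already collected at Day 1, Week +8 and Week +16. The cost is wording in two sections, one extra table and a more modest stated aim.

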### 3.0 Objectives

The primary objectives of the study are to:

1. Evaluate the safety and tolerability of anakinra in children age  $\geq 4$  years with MPS III, defined by the incidence of treatment-emergent adverse events and abnormal laboratory values, and number of subjects withdrawn due to intolerability (e.g. unable to administer SC injection to subject, worsening behaviors).
2. Evaluate the effect of anakinra on a multi-domain responder index (MDRI) as a means to determine need for dose escalation. Due to the inherent heterogeneity of disease presentation, the MDRI will measure change tailored to patient-specific symptoms. MDRI change will inform dose-finding by reflecting lack of change in clinical outcome. The MDRI will be composed of the following:
  - Sanfilippo Behavior Rating Scale (SBRS)
  - Child Sleep Health Questionnaire (CSHQ)
  - Autism Parenting Stress Index (APSI)
  - PROMIS Fatigue - Parent Proxy Custom Short Form
  - Seizures – parent reported frequency, duration, and severity
  - Movement disorder (e.g. dystonia, chorea, etc.) – parent reported frequency, duration, and severity
  - Non-communicating Children's Pain Checklist-Revised (NCCPC-R)

The secondary objectives of the study are to evaluate the effect of anakinra on:

- Individual Clinical Response (ICR) – 5 most impactful clinical problems reported by the caregiver
- Gait
- Stair climb/descent
- Sleep Diary (1-week recall)
- Sanfilippo Syndrome Stool Habit Questionnaire

The exploratory objectives of the study are to evaluate the effect of anakinra on:

- ☐ Stool microbiome
- ☐ Vineland Adaptive Behavior Scales, Third Edition (VABS-III)

## 4.0 Background

Sanfilippo syndrome, or mucopolysaccharidosis type III (MPS III), is a genetic disorder of metabolism, associated with insufficient production of a lysosomal enzyme crucial for degradation of heparan sulfate. As a consequence, buildup of heparan sulfate causes progressive, irreversible neurodegeneration. There are four variants of MPS III, distinguished by the lysosomal enzyme deficiency: Heparan-N-sulfatase (MPS IIIA),  $\alpha$ -N-Acetylglucosaminidase (MPS IIIB), AcetylCoA:N-acetyltransferase (MPS IIIC) and N-Acetylglucosamine 6-sulfatase (MPS IIID). MPS IIIA and MPS IIIB are the most common subtypes.

Unlike other types of MPS which involve considerable somatic complications, the most significant aspect of MPS III is neurodegeneration which manifests in stages of developmental disruption and decline, defined by Cleary and Wraith. Their 3-stage model involves: 1) developmental delay in cognition and language before age 3-4 years, 2) temper tantrums, hyperactivity, aggression, sleep disorder, and a further loss of cognitive and language function from age 3-4 years to age 8-10 years, and 3) loss of motor function, feeding difficulties, and seizures from age 8-10 years. Recent work has determined that there is a loss of about 15 IQ points per year in children with MPS IIIA who are younger than 6 years and that they do not surpass a mental age equivalent of 30 months. The advancing disease causes the neurobehavioral profile to meet diagnostic criteria for autism^3, and to overlap with Kluver-Bucy syndrome. A study of patients with both MPS IIIA and IIIB in several European countries found comparable patterns of disease progression in the groups, with delayed language development and cognitive decline, as well as disruptive behavior, particularly in children diagnosed before age 5.

The neurobehavioral symptoms associated with MPS III are highly disruptive and distressing to families, have a significant impact on the quality of life for the patient and family, and likely interfere with adjunctive therapeutic attempts at supporting the child. However, despite the universal acknowledgment that these neurobehavioral symptoms are a prominent concern for MPS III, these symptoms have not been the therapeutic target.

Sanfilippo syndrome is the most common form of MPS, with an incidence of about 1 in 70,000 births. However, to date no evidence-based treatments are available, which is a striking contrast to another neurodegenerative form of MPS, Hurler syndrome (MPS IH),

which is much rarer but can be arrested with hematopoietic stem cell transplantation (HSCT). HSCT was tried for MPS III, but all patients failed to obtain any benefit. A trial of Genistein, an over-the-counter supplement that apparently can lower glycosaminoglycans, such as heparan sulfate, in the urine, was recently closed due to

lack of clinical benefits. In addition, an ongoing study of caregiver preference focused on meaningful treatment benefit outcomes is underway. Focus group data indicated that caregivers prioritized symptoms of communication problems, difficult behaviors, pain, declining mobility, poor sleep and gastrointestinal issues as desired targets of potential emerging therapies. While new therapies are proliferating, there are many affected children who are ineligible for clinical trials but whose families are suffering as the disease advances and the neurobehavioral profile becomes profoundly disruptive.

